#### 2.6.3. Aim 3: Treatment acceptability

To investigate whether or not treatment acceptability differs between the treatment conditions, a one-way ANOVA with Treatment condition as the independent variable and scores on the individual treatment acceptability questions as dependent variables will be performed.

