### 1.4. Current study

The available literature shows promising results regarding both EMDR 2.0 therapy and the Flash technique. However, for EMDR 2.0 and the Flash technique, a randomized controlled trial with participants diagnosed with PTSD is still lacking. Therefore, the goal of the present study will be to investigate EMDR 2.0 and the Flash technique in a sample of participants diagnosed with PTSD, and to determine their relative effectiveness, when compared with each other and standard EMDR therapy (38) as an active control condition. We chose EMDR therapy as a comparator, because it is one of the first-choice interventions for PTSD according to the international treatment guidelines (50). This allows for direct comparison between the experimental conditions and the extensively studied EMDR therapy. The proposed study has three aims. Firstly, we will determine the differential effectiveness of EMDR therapy, EMDR 2.0, and the Flash technique. More specifically, we will investigate which of these treatment conditions is most effective in reducing (complex) PTSD symptoms and comorbid psychiatric symptoms, as well as the loss of the diagnostic status of PTSD. In addition, we will investigate whether EMDR 2.0 and the Flash technique are effective treatments, by inspecting changes in these outcomes over time. We will also determine the moderators of effectiveness. The moderators that will be investigated are PTSD symptom severity, symptoms of depression and dissociation, experiential avoidance, and the presence of a complex PTSD diagnosis. To this end, identifying potential moderators can help to indicate which treatment option is most suitable for different types of patient characteristics. Secondly, we will investigate the differential efficiency of the three treatments. Thirdly, we will investigate whether the treatments differ in terms of treatment acceptability.

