There is not enough evidence to have *a priori* expectations with regards to the differential effectiveness of standard EMDR therapy compared to EMDR 2.0 or the Flash technique. Based on the results of earlier research on EMDR 2.0 and the Flash technique [e.g., (39, 48)], we expect that all interventions will be effective in terms of a significant reduction of (complex) PTSD symptoms and loss of diagnostic status. We also expect that all interventions will be effective in reducing the symptoms associated with PTSD. Considering the moderators, we expect that participants who show higher baseline symptoms of depression, will experience more difficulties in retrieving positive memories based on studies suggesting a negative memory bias in individuals with depression (51, 52). Therefore, we expect them to benefit less from the Flash technique than from EMDR therapy or EMDR 2.0. Furthermore, we expect participants who show relatively higher levels of experiential avoidance (defined as attempts to avoid thoughts, feelings, memories, physical sensations, and other internal experiences) and symptoms of dissociation at baseline, will benefit more from the Flash technique than from EMDR therapy. The reasoning underlying this hypothesis is that during the Flash technique only brief exposure to traumatic material is needed (42). Therefore, participants who are more avoidant, or tend to dissociate, will likely have less difficulty performing the Flash technique, than EMDR therapy. Based on the results of Matthijssen et al. (39), EMDR 2.0 is expected to be more efficient than standard EMDR therapy in treating traumatic memories and PTSD symptoms. Based on the preliminary findings of Brouwers et al. (48), we expect that the Flash technique will be rated as more acceptable by patients than standard EMDR therapy.

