#### 2.3.3. Assessments

At baseline assessment (T0), the CAPS-5 will be administered by a trained therapist, along with the Life Events Checklist for DSM-5 (LEC-5). The International Trauma Questionnaire (ITQ), PTSD Checklist for DSM-5 (PCL-5), Dissociative Experiences Scale (DES), Beck Depression Inventory-II (BDI-II), Brief Symptom Inventory (BSI), and the Acceptance and Action Questionnaire-II (AAQ-II) will be administered digitally. The baseline assessment takes approximately 90 min. After the baseline assessment and the session where the treatment plan is drawn up, a 6-week treatment phase commences during which participants fill out questionnaires weekly prior to the treatment sessions (T1-6). Questionnaires include the PCL-5, BDI-II, BSI, and AAQ-II and take approximately 30 min in total to complete. After the first treatment session (T2), a questionnaire about treatment acceptability is administered. After the treatment phase, a 12-week phase commences where no actual treatment is delivered, but participants fill out the PCL-5, BDI-II, BSI, and AAQ-II bi-weekly (T7-12). The treatment acceptability questionnaire is administered again at T7. The CAPS-5, ITQ, and DES are administered 4 weeks after treatment is completed (T8), and 12 weeks after termination of treatment (T12). To minimize missing data, reminders will be sent out to the participants to fill out the questionnaires. For a complete overview of the timing of the interventions and assessments, see Figure 1.

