##### 2.4.2.5. Treatment acceptability

Treatment acceptability is assessed with four questions based on Tarrier et al. (78) and Devilly (79) which measure several facets which could be grouped under treatment acceptability. Three questions are: “How did you experience treatment?” The answer options range from 1 (very unpleasant) to 7 (very pleasant), from 1 (very intrusive) to 7 (not intrusive at all), and from 1 (very tiring) to 7 (not tiring at all). The fourth question is: “How likely is it that you would recommend the treatment to someone with the same symptoms?,” with answer options that range from 1 (very unlikely) to 7 (very likely). As the questions combined have not been validated as a questionnaire measuring the full concept of treatment acceptability, the items will be scored and interpreted separately instead of computing a total score.

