## 3. Discussion

The current study may have several clinical implications. For instance, if our hypotheses that EMDR 2.0 and the Flash technique are effective treatments for PTSD are supported, it would offer therapists additional treatment options. Furthermore, if EMDR 2.0 is found to be more efficient than EMDR therapy, we would may be able to treat more patients within the same timeframe, which would reduce patient burden, as well as wait-list duration and treatment costs. This is necessary because PTSD is a major public health problem that incurs high healthcare costs (2). Another implication is that, if the Flash technique is found to be more acceptable than EMDR therapy, the application and dissemination of the Flash technique could reduce patient burden. Similarly, since treatment dissatisfaction appears to be related to treatment dropout, more acceptable treatments will likely improve treatment engagement and reduce attrition (78, 87, 88). Finally, the identification of moderators of treatment response would help match patients with the most suitable treatment options based on their characteristics.

The current study also has several scientific implications. One implication is that the current study is likely to provide a foundation for future research on EMDR 2.0 and the Flash technique, and their applicability in the clinical field, as well as future research on mechanisms of action. Furthermore, the present study could contribute to the collection of data on possible pre-treatment factors that moderate the effectiveness of PTSD treatment (89).

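### The acceptability analysis in 2.6.3 is a three-group one-way ANOVA, which does not test the stated Flash-versus-EMDR hypothesis and cannot use the two ratings together

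*Protocol article*

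**What the plan says.** Section 1.4 (Current study) puts the acceptability question in two ways. The aim is general: "we will investigate whether the treatments differ in terms of treatment acceptability". The hypothesis is directional and concerns one pair: "we expect that the Flash technique will be rated as more acceptable by patients than standard EMDR therapy". The Discussion draws a clinical implication, lower patient burden, from that same pair.

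Section 2.4.2.5 defines four single items scored 1 to 7 and says that "the items will be scored and interpreted separately instead of computing a total score". Section 2.3.3 collects them twice: "After the first treatment session (T2), a questionnaire about treatment acceptability is administered", and "The treatment acceptability questionnaire is administered again at T7".

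The whole analysis in section 2.6.3 is "a one-way ANOVA with Treatment condition as the independent variable", with the score on each single item as the outcome. It names no contrast and no occasion.

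Two other statements bear on this. Section 2.6 sets intention to treat and prefers multilevel models to repeated-measures ANOVA because they can include participants with incomplete data. The Discussion expects more acceptable treatments to reduce attrition, "since treatment dissatisfaction appears to be related to treatment dropout".

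**The concern.** A one-way ANOVA over three conditions asks whether any of the three means differ. It gives no answer about Flash against EMDR, which is the comparison the authors predict and intend to interpret. A significant result could come entirely from EMDR 2.0.

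The method also has no within-person factor. It can be run on one occasion at a time, but it cannot use the session-1 and T7 ratings jointly. Four items at two occasions allow up to eight F tests, and none is designated as the one that bears on the hypothesis.

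Finally, it uses observed scores only. Among the trial's outcomes, acceptability is the one the protocol itself ties to dropout, yet it is analysed without the kind of model that section 2.6 prefers for incomplete data. If dissatisfied patients are missing at T7, and more of them in the less acceptable arm, the T7 difference between arms shrinks.

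**Working it through.** **The plan's own figure.** Section 2.5 sizes the trial for pairwise CAPS-5 comparisons; no figure is given for acceptability. A two-sided t-test with d = 0.65, alpha = 0.05/3 and power 0.80 needs 52 per arm. With a quarter of the variance explained, 52 × 0.75 = 39 per arm, 3 × 39 = 117, and 117/0.90 = 130. The stated 39, 117 and 130 reproduce, so there is no numerical error here. I use 39 per arm below.

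**Does the F test answer the pairwise question?** For three arms of n, with means in SD units, the noncentrality is λ = n × Σ(mean − grand mean)², on 2 and 3n − 3 = 114 degrees of freedom. The 5% critical F is 3.08. The effect size for the items is an assumption; I borrow 0.65 from section 2.5.

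- Flash = EMDR = 0 and EMDR 2.0 = −0.65: λ = 39 × 0.65² × 2/3 = 10.99, and the rejection probability is 0.84.

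Here the stated hypothesis is false, and the planned test is still significant 84% of the time.

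**Is power the issue?** For the direct contrast the noncentrality is d × √(n/2). With an assumed d = 0.50 this is 0.50 × √19.5 = 2.21.

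| Position of EMDR 2.0 | λ | Omnibus F at 0.05 | Flash-EMDR contrast at 0.05 |
|---|---|---|---|
| Midway between Flash and EMDR | 4.875 | 48% | 59% |
| Equal to one of them | 6.50 | 61% | 59% |

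At alpha = 0.0167 the contrast has 42%. So the contrast has no general power advantage.

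**How much could the T7 difference be understated?** All inputs are assumptions except 18%, which section 1.1 gives as a published EMDR dropout figure. I take a true Flash-EMDR difference of 0.50 SD at both occasions, a within-patient correlation of 0.6, a logistic slope for missingness of −1.2 per SD of the rating, and no T7 rating from those who drop out. Large-sample simulation gives:

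| Missing at T7, EMDR / Flash | Missingness depends on | Observed T7 difference | Estimate using both occasions |
|---|---|---|---|
| 18% / 8% | session-1 rating | 0.44 | 0.50 |
| 18% / 8% | T7 rating itself | 0.41 | 0.44 |
| 12% / 8% | session-1 rating | 0.48 | 0.50 |
| 10% / 10% | either | 0.50 | 0.50 |

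A second model lets the dropout difference arise from acceptability itself, with a correlation of 0.3 to 1.0 between dropout liability and poor acceptability. The observed difference then runs from 0.49 down to 0.39 when EMDR dropout is 10%, and from 0.48 down to 0.34 when it is 18%.

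**The case against.** The ANOVA fits the aim as section 1.4 words it, and section 2.6.3 repeats that non-directional wording. Follow-up contrasts are commonly left to an analysis plan, and this is a condensed article. With three groups, a significant F followed by unadjusted pairwise tests controls the familywise error; for the Flash-EMDR pair that sequence has power of 46% (EMDR 2.0 midway) to 51% at d = 0.50. Acceptability is a secondary outcome. All of this stands, and it limits the weight of the point. It does not remove the mismatch: the article states a pairwise hypothesis and fixes a test that does not address it.

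Three stronger readings are tempting, and the document does not support them.

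- **That the T7 analysis will lose the patients who left because treatment was unpleasant.** Nothing says that patients who stop treatment are not asked at T7. The analysis is by intention to treat, the questionnaires are digital and reminders are sent. The Discussion links dissatisfaction to treatment dropout, not to missing questionnaires. The session-1 rating is also little exposed to dropout.
- **That the omnibus test wastes power.** It does so only if EMDR 2.0 lies between the other two arms. Otherwise it is level or slightly ahead, and the contrast's 59% depends on giving one pair the full 0.05.
- **That a mixed model would restore the true difference.** It does so only where missingness is explained by the session-1 rating.

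**Conclusion.** The point holds as a mismatch between hypothesis and test. It rests on the article's own wording and needs no assumption; the 0.84 only illustrates it and depends on the assumed 0.65 SD. That a one-way ANOVA cannot combine the two ratings follows from the method named.

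The understated T7 difference is a conditional risk. It requires that patients who stop treatment also give no T7 rating, and that more do so in the less acceptable arm. Under 18% against 8%, a true 0.50 SD would appear as about 0.41 to 0.45, depending on what drives the loss. With equal loss there is no bias. The item effect sizes, the correlation and the dropout model are not in the document.

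The change is worth making because it is cheap and settles, before the data are seen, which comparison decides the hypothesis.

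**What to change.** In section 2.6.3, replace the ANOVAs with one mixed model per item over both occasions, with condition, occasion and their interaction. Name the Flash-EMDR contrast as the test of the hypothesis in section 1.4, and report the other two pairs as secondary. Report treatment dropout and missing T7 ratings by arm beside the T7 estimate. Say that the model removes bias at T7 only so far as the session-1 rating explains who is missing, and only partly otherwise.

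The cost is a few sentences and slightly more modelling. No new data are needed, and design and sample size stay as they are. The price is that the EMDR 2.0 acceptability comparisons become secondary.

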### 2.7. Data management and monitoring

To maintain confidentiality, data will be stored digitally on secured servers of the Altrecht Academic Anxiety Center. No analog data will be collected. Every participant will get an identification number, based on the order of inclusion. The data will be accessible by the principal investigator and research assistants involved in the study, affiliated with the Altrecht Academic Anxiety Center. Personal data will be handled according to the European General Data Protection Regulation. After consulting the guidelines posted by the European Medicines Agency, the installation of a Data Monitoring Committee was not deemed necessary. Pseudonymised data will be accessible to authors not affiliated with Altrecht. In accordance to the Dutch Medical Scientific Research Law, the trial will be suspended when there is sufficient ground that continuation of the study will jeopardize subjects’ health or safety. Serious adverse events (SAE’s) will be reported to the principal investigator within 24 h. SAE’s will also be reported to the Medical Research Ethics Committee (MREC) “NedMec” that approved the protocol.

## 3. Discussion

The current study may have several clinical implications. For instance, if our hypotheses that EMDR 2.0 and the Flash technique are effective treatments for PTSD are supported, it would offer therapists additional treatment options. Furthermore, if EMDR 2.0 is found to be more efficient than EMDR therapy, we would may be able to treat more patients within the same timeframe, which would reduce patient burden, as well as wait-list duration and treatment costs. This is necessary because PTSD is a major public health problem that incurs high healthcare costs (2). Another implication is that, if the Flash technique is found to be more acceptable than EMDR therapy, the application and dissemination of the Flash technique could reduce patient burden. Similarly, since treatment dissatisfaction appears to be related to treatment dropout, more acceptable treatments will likely improve treatment engagement and reduce attrition (78, 87, 88). Finally, the identification of moderators of treatment response would help match patients with the most suitable treatment options based on their characteristics.

The current study also has several scientific implications. One implication is that the current study is likely to provide a foundation for future research on EMDR 2.0 and the Flash technique, and their applicability in the clinical field, as well as future research on mechanisms of action. Furthermore, the present study could contribute to the collection of data on possible pre-treatment factors that moderate the effectiveness of PTSD treatment (89).

There are some limitations of the study design that need to be addressed. First, a limitation includes the risk of missing data, due to numerous measurement occasions after the treatment phase. However, by using a statistical method that handles missing data well, we mitigate the impact of missing data on the statistical power. Furthermore, a limitation of the present study is that the participants are not blinded to their treatment conditions. This makes the design susceptible to expectancy effects of the participants. However, we do not anticipate that these expectancy effects will be stronger for one condition than for another, and the randomization process should account for an even distribution if these effects would occur. Another limitation is the absence of an inactive control condition. To this end, on the one hand, our study is a suboptimal design for testing the hypotheses that the experimental conditions are effective treatments for PTSD. In contrast, the active control condition in this study has been frequently compared to wait-list control conditions (7, 8), showing that EMDR therapy was more effective in the treatment of PTSD than wait-list control conditions. Therefore, we can assume that when EMDR 2.0 and the Flash technique have comparable effect sizes in comparison with EMDR therapy, these interventions are likely to be more effective than a waitlist control condition in the treatment of PTSD. Finally, a limitation of the present study is that the design and sample size will not yield enough statistical power to detect small effect sizes when comparing the treatment conditions or when investigating moderators of effectiveness.

The study design also has several strengths. First, a wide array of outcomes of comorbid symptoms to PTSD (e.g., symptoms of depression and dissociation) will be assessed. Therefore, it is likely that the current study will add to the existing evidence of the effectiveness of EMDR therapy beyond PTSD symptoms (7, 8), and will allow us to compare EMDR 2.0 and the Flash technique with other trauma-focused treatments on these outcomes. Secondly, we will investigate whether the treatment results are maintained over a longer period, by monitoring the symptoms over the course of 12 weeks after treatment termination. Thirdly, therapists record their sessions on video and measure the time they spent on the intervention. Although this is originally incorporated in the procedure to assess treatment fidelity and treatment efficiency, this practice also serves to motivate therapists to optimally use the session time for the intervention and to not elaborate on peripheral matters, improving protocol adherence. Finally, we assess treatment efficiency not only using the intervention time needed to decrease subjective units of disturbance scores, but also by assessing the number of sessions needed to improve in symptomatology. Therefore, the current study may provide better insight into which treatment is most efficient in reducing PTSD symptoms and achieving clinically significant changes.

In conclusion, we believe that the proposed trial is of clinical and scientific relevance given that it is the first RCT to investigate EMDR 2.0 and the Flash technique in a sample of patients diagnosed with PTSD. In addition to focusing on effectiveness, the trial also investigates the treatment efficiency, acceptability, and moderators of effectiveness.

## Ethics statement

The studies involving humans were approved by the Medical Research Ethics Committee NedMec (NL79163.041.22). Important protocol modifications and study progress will be communicated to MREC NedMec according to their regulations. The studies were conducted in accordance with the local legislation and institutional requirements. The participants provided their written informed consent to participate in this study. A participant insurance was not deemed necessary by the MREC NedMec because of negligible risks associated with participation. Patients participating in the trial will not pay for the treatment they receive. Patients who still show symptoms after participation in the trial has been completed, will be offered additional treatment in our mental healthcare institution. We aim to publish the results of the current study in peer-reviewed journals, regardless of the outcome of the study. In addition, the results will be disseminated at national and international symposia and conferences. To be eligible for authorship, the authors will be required to have made substantive contributions to the design, analyses, conduct, interpretation, and/or reporting of the trial. Before inclusion, participants are informed of the study procedure using an information brochure. If they have had sufficient time to think (at least one week) and agree to participate, they will sign an informed consent form. Participants are informed of their right to withdraw from the study at any time. In accordance to the Dutch Medical Scientific Research Law, the trial will be suspended when there is sufficient ground that continuation of the study will jeopardize subjects’ health or safety. Serious adverse events (SAE’s) will be reported to the principal investigator within 24 h. SAE’s will also be reported to the Medical Research Ethics Committee (MREC) “NedMec” that approved the protocol.

